#### Intervention

This RTW intervention uses a multicomponent approach grounded on behavioural change techniques (BCTs) to promote early and positive communication between the worker and the person managing their sick leave. The overall aim is to reduce the number of days on long-term sickness and enable a successful RTW. The intervention comprises of 2 toolkits — an employer and worker RTW toolkit. Both toolkits are self-led interventions used by the employer (or manager) and the worker themselves. The guidance and resources in the toolkits for the worker and the employer mirror each other to ensure both receive the same messages and to encourage transparency.

Once participants have been consented into the intervention, they will be able to access the toolkits through a secured website with a code provided by the research team. The toolkits include three step-by-step approaches to be used at different stages of the workers’ RTW process: step 1 managing initial sick leave, step 2 preparing to RTW and step 3 managing back at work. Additionally, the worker toolkit is supported by a coaching component, and the employer toolkit is supported by an upskilling training webinar session. Both toolkits have been cocreated with workers with mental health and RTW experience and managers and employers from SMEs and LEs. Both toolkits have also been developed with input from the charity Mind as well as evidence from the scientific literature and best practice guidelines for the UK (NICE, 2019). PROWORK toolkits are grounded in the implementation intentions theory [21], conservation of resources (CoR) theory [22] and communication accommodation theory [23]. In addition, the worker toolkit is also grounded in the implementation intentions [24], transtheoretical model of change [25] and the socio-cognitive theory [26]. The cognitive behavioural elements (e.g. unhelpful thinking worksheet) in the toolkit are also informed by principles of problem-solving and cognitive behavioural approaches [27–29]. Table 2 provides a description of each intervention components, whilst Fig. 2 outlines the logic model.

**Table 2 Tab2:** Description of intervention components

Intervention component	Description	
**Management of sickness absence and RTW**	**Worker toolkit** - Education ○ How and when to use the toolkit ○ Sick leave and wellbeing - Step-by-step guidance of how to self-manage ○ Sickness absence ○ Preparing to RTW ○ Being back at work - How to build confidence in managing mental health? - How to prepare to RTW? - Knowledge of different signs of low mental wellbeing - Where to find support to improve my mental health? - What to do for a sustainable RTW? **Barrier identification** - Is there anything that might stop you from using the toolkit? - Is there anything that might stop you from having a successful RTW? - How can you overcome these challenges? **Behavioural change techniques** - Introduction to step-by-step techniques to improve health and build confidence to RTW - Introduction to styles of thinking and management of unhelpful thinking - Introduction to SMART goals - Using checklists and activities to track changes and plan ahead	**Employer toolkit** - Education ○ How and when to use the toolkit? ○ How to apply a person-centric approach? ○ Sick leave and mental wellbeing - Step-by-step guidance of how to manage ○ Managing sickness absence ○ Preparing for worker’s RTW ○ Managing the worker back at work - How to be in the right mindset to manage the RTW well? - How to develop positive communication skills? - Knowledge of different signs of low mental wellbeing - Where to find support to manage worker’s RTW? - What to do for a sustainable RTW? **Barrier identification** - Is there anything that might stop you from using the toolkit? - Is there anything that might prevent you from applying positive communication techniques? - How can you overcome these challenges? **Behavioural change techniques** - Introduction to step-by-step techniques to build confidence and manage RTW positively - Introduction to positive communication techniques - Introduction to goal setting - Using checklists and activities to track changes and plan ahead
**1-h worker coaching session**	- Three workplace coaching sessions based on goal setting and problem-solving skills to support the worker during their sick leave and RTW - Goal setting and revision of previous and future goals and their outcomes - Identification of challenges and facilitators of each of the goals - Revision of activities and planning of the next steps	
**20-min employer training webinar**	- Initial training module to inform the person managing the sick leave and RTW of a worker of how to have conversations about mental health at work and help the worker feel comfortable and confident about having those conversations	
**Prompts**	- Prompts offered by researcher to encourage worker and employer to use the toolkit	
**Intervention checklists**	- Completion of checklists at each of the sickness absence and RTW stages - Rate confidence to RTW - Rate mental wellbeing	
	- Researcher to ask participants to send their completed checklists for compliance	
**Group messaging**	- To be used as a platform to contact employees to record their RTW date

**Fig. 2 Fig2:**
[figure not shown]
PROWORK logic model

### Workers

Workers on sick leave will receive the intervention until RTW or 4 months (last follow-up) from when the worker has completed baseline measures. PROWORK includes a step-by-step action-oriented toolkit that provides guidance and support from initial absence to post RTW. Three workplace coaching sessions based on goal setting and problem-solving will be offered to worker by a trained project researcher over the phone. These will be delivered at three timepoints throughout the intervention: (1) at the start, to support making contact, to coach the participant in the use of the resources, to build a relationship with the participant and to direct the participant to external resources available in the toolkit; (2) at 2 months to coach them for preparation to RTW, or if they have returned to work, and then to coach them in adjusting back to work; and (3) at 3 months to either coach them for preparation to RTW or if they have returned to work and then to coach them in adjusting back to work. The coaching sessions aim to motivate and support workers to use the RTW toolkit, to help them with any activities they might feel stuck with and to discuss their action plan to avoid any relapse. During these sessions, and as part of the process evaluation, the workplace coach will ask about what resources are the worker finding more useful and what are the benefits of using this toolkit.

To reinforce the message of having regular communication with the workplace whilst on sick leave, the worker will have the option to contact the workplace coach (i.e. project researcher) when needed either by email or phone call.

### Employers

Employers will have access to a RTW training video at the start of the intervention study, prior to recruiting workers on sick leave. The key workplace person (e.g. the line manager) responsible for managing a worker on sick leave will receive an employer version of the toolkit and provided with advice on when and how to use it with a worker. For those individuals who are managing more than one worker on long-term sick leave, they will receive an email from the researcher at the start of each worker on long-term sick leave, to remind them to use the toolkit (once they had done the webinar training).

#### Active control group

To compare the effects of the intervention against usual practice, organisations allocated into the control group will be asked to continue with their usual procedures, and no training or guidance will be offered. Participants in the control group will be asked to complete the same measurements as those in the intervention group and at the same timepoints. At the end of the PROWORK study, organisations in the control group will receive a report evaluating their current RTW policies and procedures, access to the line manager training and hard copies of both toolkits.

#### Outcome measures

Primary and secondary outcome measures will be collected at baseline, 2 months and 4 months. Outcome measures will be collected for both workers and managers. Outcome measures have been grouped as process outcomes and research outcome measures (see below), and they will be collected using Qualtrics; data and personal details will be stored according to the General Data Protection Regulation (GDPR, 2016/679) and research governance guidelines. A summary of the outcome measures at the various time points is provided in Table 3. Qualitative interview data will be collected either over the phone or using online conferencing facilities. Both full-return (defined for this study as working the same days or hours per week as before sickness absence in an identical or equivalent role for at least 4 weeks) and partial RTW (defined as working any number of hours in any role) data will be collected via text messages.

**Table 3 Tab3:** Schedule of process and research outcome measures

Measured outcome	Assessment tool	Pre-randomisation	Baseline	Month 1	Month 2	Month 3	Month 4
Process outcomes							
Long-term sickness absence data for the past 12 months	Reports review	**X**					
Frameworks (sickness absence policy, return-to-work policy, mental health training and support)	Policy review	**X**					
Number of workers on (a) sick leave (≥ 8 days) and their reasons and (b) that employers have contacted to take part in the study (until the end of the study)	Checklist		**X**	**X**	**X**	**X**	**X**
Number of persons responsible for managing the sick leave and return to work (a) consenting to take part and (b) attending the training	Checklist	**X**					
Toolkit use	Volute records and interview		**X**				**X**
Feasibility and acceptability of intervention	Interview						**X**
Toolkit use	Interview						**X**
Research outcome worker							
Workers sick leave	Self-reported number of days						**x**
Depression	Patient Health Questionnaire- 9		**X**		**X**		**X**
Anxiety	General Anxiety Disorder-7		**X**		**X**		**X**
Sick leave duration	Number of days on sick leave		**X**		**X**		**X**
Self-efficacy to RTW	11-item Return-to-work Self-Efficacy Scale		**X**		**X**		**X**
Readiness to RTW	13-item Readiness to Return to work		**X**		**X**		**X**
Readiness to stay at work	9-item Readiness to Stay at Work Scale		**X**		**X**		**X**
Workplace communication	6-item Workplace Health Communication Scale		**X**		**X**		**X**
Work productivity	Work Productivity and Activity Impairment: General Health v2.0 (WPAI:GH)				**X**		**X**
Job satisfaction	A 1-item job satisfaction scale		**X**		**X**		**X**
Intention to use toolkit	4-item Toolkit Use at coaching session		**X**	**X**	**X**		
Health related quality of life	Euro-QOL — five-dimension scale		**X**		**X**		**X**
Demographics	Self-reported questionnaire		**X**				
RTW actions	Adaptation of the line manager behaviour questionnaire		**X**		**X**		**X**
Research outcomes employer							
Mental health experience	1-item questionnaire		**X**				
Sickness absence management training	1-item questionnaire		**X**				
LTSA and RTW management experience	1-item questionnaire		**X**				
Demographics	Self-reported questionnaire		**X**				
Actions to support RTW	The measure for supervisors to support return to work (SSRW)						**X**

#### Trial process-related outcome

Organisational data collection pre-randomisation is as follows:Summary of long-term sickness absence data for the past 12 months (only total numbers and % by reasons)Organisation size and sectorCopies of sickness absence policy and frameworksCopies of the work policy and frameworksDetails on mental health training and support available for managers

Organisational data collection post-randomisation and the duration of the study are as follows:Number of workers on sick leave (≥ 8 days) and their reasonsNumber of workers that employers have contacted to take part in the studyNumber of workers consenting to take partNumber of workers using the toolkit (data collected at interviews and website use)Number of persons responsible for managing the sick leave and RTW of workers consenting to take partNumber of persons responsible for managing the sick leave and RTW of workers attending the trainingNumber of persons responsible for managing the sick leave and RTW of workers using the employer toolkit (data collected at interviews and website use)

##### Coverage (recruitment and attrition)

Where possible, data on reach of study participation advertisement, expressions of interests, recruitment, participation and drop-out for all participants.

##### Toolkit use/adoption

The PROWORK website has an in-built Google Analytics system, which will provide metrics information such as number of visits to the site per day, behaviour of viewers once on the website (i.e. which pages they visited), where most of the traffic to the toolkit website came from, and the percentage of returning participants.

### Trial feasibility and acceptability-related outcomes

We will collect data on the following:Willingness of organisations to take part (baseline) and retention through follow-up with reach, uptake and completion as primary endpoints.Proportion of workers on sick leave referred to pilot study (> 50% green for main trial to go ahead, 30–50% amber; < 30% red).Proportion of workers and line manager participating in both control and intervention groups (worker: > 50% green, 30–50% amber; < 30% red)For intervention worker participants, short worker interviews will be conducted at each coaching session (at intervention start, 2 months and 3 months) to explore use of the toolkit.At 4 months (end of intervention), an interview will be conducted with both worker participants and line manager/RTW contacts to ask them about their engagement, usage and the effectiveness of the toolkit. Information regarding barriers and facilitators to implementation, functionality and interest in on-going usage will also be assessed.At the end of 12-month study period, organisational stakeholder will be interviewed to explore their perceived benefits of the intervention (engagement, usage, functionality and the effectiveness of the toolkit), as well as barriers/facilitators to implementation, interest in on-going usage and whether the intervention could form part of any workplace RTW policies.Costs associated with toolkit website build and delivery, training delivery, coaching sessions and other associated costs will be collected.

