## Background

In Britain, mental health issues increasingly account for a significant proportion of long-term sickness absence from work [1], and those who are absent for 6 months or longer have less than a 50% chance of ever returning to employment [2]. Sickness absence associated with poor mental health costs UK employers £7 billion each year [1], and a recent report by the Office for National Statistics (2019) [3] suggests sickness absence due to poor mental health is on the rise (12.4% in 2018 compared to 9.1% in 2009). The cost of sickness absence is not at an economic level only, as there are major social, psychological and financial implications for individuals on sick leave and for those unable to RTW [4]. These include inactivity, isolation, reduced workability and productivity [5–8], with reduced wellbeing and impaired self-image leading to the individual potentially withdrawing from society and support networks [5]. Long-sickness absence is also a predictor of disability pension, higher risk of unemployment and job termination [9]. Therefore, early intervention to support a worker’s RTW is not only cost-effective for the employer (e.g. in terms of reduced turnover, recruitment costs, retention of knowledge) but also is vital for workers’ health and wellbeing.

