#### Participant recruitment, inclusion criteria and consent

Within participating organisations, workers (over 18 years of age) that go on sick leave for at least 8 days (or from issue of fit note) and up to 8 weeks (50 days) and/or the person managing their sickness absence are eligible to participate. Sickness absence must be associated with either poor mental wellbeing or where poor mental wellbeing may be a comorbidity [14]. Once the worker on long-term sick leave is identified by the organisation, both the worker, and their manager, will be sent a detailed information sheet about the study so that they can make an informed decision about their participation. Those interested in taking part will contact the research team directly either by phone or email, at which stage they will be consented by the research team.

Workers on long-term sick leave will not be eligible to participate in PROWORK if they are on sick leave (a) with a psychotic episode such as schizophrenia, or with substance abuse, (b) whilst under formal investigation for misconduct or in the formal process of disciplinary action, (c) due to cancer and signed off work for at least 6 months and (d) due to a neurological condition (e.g. multiple sclerosis, Parkinson, dementia).

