### Process outcomes

The number of organisations agreeing to participate in the trial will be summarised in terms of their size, sector, sick leave and RTW polices and number of workers who were on long-term sick leave in the past 12 months prior to the start of the study.The number of worker participants identified on long-term sick leave and the number recruited into the study will be reported, along with the number of participants followed up at each timepoint. Withdrawals (and where possible, reasons for withdrawals) will be reported.Difference in recruitment uptake rate and follow-up rates at each time point will be compared between the intervention and control arms.As organisations of different sizes are taking part, it is likely there will be some imbalance between participants in each treatment arms on one or more baseline characteristics. Baseline comparisons will be carried out to detect any substantial differences between participants recruited from the control and intervention arms. This will be done by scrutinising the baseline data for any serious imbalances in observable baseline variables and the trends of the imbalance if any. The recruitment rates will also be estimated and compared between the control and intervention arms. The size of any imbalances will be examined, in addition to evidence of systematic selection bias in the types of patients being recruited in control versus intervention armsKey baseline characteristic will be compared between those participants followed up and those lost to follow-up at each timepoint.Intervention fidelity will be assessed by the log in and downloads of the toolkits. Successful adherence is defined as at least 60% download of the total toolkit by workers and employers (i.e. those with a responsibility for managing RTW) and at least 60% completion of the activities/checklist in total.Following the guidance from the COREQ-32 checklist [45], qualitative interview data for the process evaluation will be recorded, transcribed verbatim and coded following the principles of thematic analysis [46].The Theoretical Domains Framework [43], and the normalisation process theory [47], will be used to guide thematic analysis of the qualitative data. The findings will be supplemented with observations made by the researchers throughout the implementation of the intervention. Collectively, these will provide information on the acceptability of the trial measurements and the intervention.Survey data for the process evaluation will be summarised using means, standard deviations, medians and ranges for continuous variables and counts and percentages for categorical variables.The pilot data will provide information on the parameters needed for a realistic sample size calculation (mean and standard deviation) for a future, main cluster RCT.

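### The referral progression criterion divides by all workers on sick leave rather than by eligible workers, so its traffic light partly measures case mix

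*Protocol article*

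**What the plan says.** The section on trial feasibility and acceptability-related outcomes sets two traffic-light rules. The first is the "Proportion of workers on sick leave referred to pilot study": above 50% is green, the level at which the main trial proceeds, 30% to 50% is amber and below 30% is red. The second is "Proportion of workers and line manager participating in both control and intervention groups (worker: > 50% green, 30–50% amber; < 30% red".

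The section on the trial process-related outcome lists what organisations record after randomisation. It includes how many staff are absent for 8 days or longer (with reasons), how many of them the employer has contacted about the study, and how many consent. The first of these counts is not restricted by reason.

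The section on participant recruitment limits entry to absences of 8 to 50 days, and adds: "Sickness absence must be associated with either poor mental wellbeing or where poor mental wellbeing may be a comorbidity". It then lists four exclusions: psychotic illness or substance abuse, misconduct or disciplinary procedures, cancer with a long sign-off, and neurological disease.

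On adherence, the Process outcomes section states: "Successful adherence is defined as at least 60% download of the total toolkit by workers and employers". It also asks for 60% completion of activities and checklists over the whole toolkit. The Intervention section divides the toolkit into "step 1 managing initial sick leave, step 2 preparing to RTW and step 3 managing back at work", and Table 2 has checklists completed stage by stage.

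**The concern.** A referral criterion should show whether organisations pass the study on to the workers who could join. With every absent worker in the denominator, it also reflects how many absences happen to be eligible, which organisations do not control. Two sets of organisations with the same referral performance could receive different colours, and the first rule ties green explicitly to the main trial going ahead. An organisation could also raise its figure by sending information to workers who cannot enter.

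The completion part of the adherence measure has a milder form of the same problem. The third toolkit step applies only after return to work, so the score depends partly on return-to-work status, which is the primary research outcome.

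**Working it through.** **Inputs.** Bands of 50% and 30%, and the 60% adherence cut, are from the article. They are chosen cut-offs without a formula, so there is no figure to reproduce. Two quantities are not given and are varied below:
- e, the share of workers absent 8 days or more who are eligible;
- r, the share of eligible workers who are referred.

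**Referral.** Assuming that only eligible workers are referred:

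observed proportion = e × r, with maximum e (at r = 100%).

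The referral rate must exceed 0.50/e for green and reach 0.30/e to avoid red.

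| Eligible share e | r = 100% | r = 80% | r = 60% | r needed for green |
|---|---|---|---|---|
| 20% | 20% red | 16% red | 12% red | not attainable |
| 30% | 30% amber | 24% red | 18% red | not attainable |
| 40% | 40% amber | 32% amber | 24% red | not attainable |
| 50% | 50% amber | 40% amber | 30% amber | not attainable |
| 60% | 60% green | 48% amber | 36% amber | above 83.3% |
| 70% | 70% green | 56% green | 42% amber | above 71.4% |
| 100% | 100% green | 80% green | 60% green | above 50% |

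Down the 80% column, one referral performance runs through all three colours. With e ≤ 50% green is out of reach at any r, because green requires more than 50%. With e < 30% the result is red at any r. With an eligible-only denominator the observed proportion equals r, and every row would read like the last one.

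**Adherence (completion part).** Let s be the share of activities in stages the worker did not reach.

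maximum completion = 1 − s; completion needed among reachable activities = 0.60/(1 − s).

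The article gives no activity counts per step. Assuming equal thirds:
- All three steps reached: s = 0, so 60% of the reachable activities is enough.
- Steps 1 and 2 reached: s = 1/3, so the maximum is 66.7% and 0.60/0.667 = 90% of the reachable activities is needed. Completing 80% or 85% of them gives 53.3% or 56.7% and fails.
- Step 1 only: s = 2/3, so the maximum is 33.3% and the worker cannot pass.

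Without that assumption, a worker who completes everything in steps 1 and 2 fails only if step 3 holds more than 40% of the activities (1 − 0.40 = 0.60).

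**The case against.** The strongest reply is that the article uses workers on long-term sick leave as shorthand for its target group. On that reading the denominator is already the eligible workers, and because absence reasons are recorded it could largely be built. The comorbidity clause is also broad, so the eligible share may be high.

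The breadth of the clause stands: the share is unknown, and if it is well above half the distortion shrinks. The shorthand reading does not settle the matter. The logged count is defined by duration of absence alone, and the rule does not call on the recorded reasons. Choosing between the two denominators once results are known would undo the purpose of fixed thresholds.

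A reader might infer more than the article supports, in three ways.
- **A feasible trial would read as red.** The Background says "sickness absence due to poor mental health is on the rise (12.4% in 2018 compared to 9.1% in 2009", and taking 12.4% as the eligible share would give red even at full referral. That figure is national, is not specific to absences of 8 days or more, and leaves out comorbidity. It is not the eligible share.
- **Full toolkit users would be classed as non-adherent.** Under equal thirds, a worker who completes steps 1 and 2 scores 66.7% and passes. The download part is not tied to stage. Adherence carries no traffic light, so it cannot turn the go decision.
- **The other gaps are errors.** The unstated participation denominator, the lack of a manager threshold and the lack of a retention light are detail that a condensed article may leave to the full protocol, or matters of preference.

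**Conclusion.** The point holds for the referral criterion. As worded, it measures eligible share times referral rate. It therefore caps the result at amber when 50% or fewer of the logged absences are eligible, and at red when fewer than 30% are, however well organisations refer. This rests on two things: that the denominator is the logged count of absences of 8 days or more, and that only eligible workers are referred. The article does not let anyone say which colour would result, because the eligible share is not stated.

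The adherence point is secondary. The completion score is partly tied to return-to-work status. Under the equal-thirds assumption, only workers confined to one step are certain to fail, while those who reached step 2 face a 90% requirement on what they could do. It is a fidelity measure and not a go/no-go rule.

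**What to change.** Keep the bands and define the ratios before the referral counts are examined.
- **Criterion 1:** workers sent study information, divided by workers on sick leave who meet the article's entry criteria as far as the employer can determine from the recorded reason and duration of absence. The proportion of all absent workers can still be reported as a description of reach.
- **Criterion 2:** workers consenting, divided by workers sent information, by arm. This makes the two criteria successive steps of one recruitment flow.
- **Adherence:** keep the 60% measure over the whole toolkit, and also report completion over the stages each participant reached.

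The cost is mainly wording, plus some added recording: employers would log duration and known exclusions alongside the reason. Comorbid poor mental wellbeing may be incompletely known to them, so the number of workers whose eligibility could not be determined should be reported next to criterion 1.
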